### Data analysis

Data were prospectively collected by local staff both in intervention and in control groups (physician and nurses who were trained in two pre-study educational events). We did not use incentives for the local staff.

The analysis will be performed by the research team. In addition to common descriptive statistics (Fisher exact and Kruskal Wallis test for categorical and continuous variables, respectively), that will be performed at the cluster level, the differences in the rate of in-hospital deaths and unscheduled admissions across groups and according to each variable under study will be evaluated using random-effects logistic regression, thus accounting for the clustering effect [30-33]. Variables will be included if significant at the 0.10 level (backward approach), with the exception of age which will be forced to entry. The presence of multicollinearity, interaction and higher power terms will be assessed to check final model validity. Patients who died during the study will be excluded from the regression model evaluating unscheduled readmissions because they could not be re-admitted.

Statistical significance will be defined as a two-sided p-value < 0.05. All analyses will be intention-to-treat and will be carried out using STATA statistical software, version 8.2 (Stata Corporation, College Station, Texas, 2003).

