### Objectives

The primary objective of the trial was to evaluate the effectiveness of the implementation of clinical pathways for hospital treatment of heart failure among a sample of Italian hospitals. Our hypothesis was that the clinical pathways should be more effective than usual care in treating patients admitted in hospital for heart failure and that the clinical pathways should reduce patients' mortality during the stay and that they should improve patients' outcomes at discharge.

Secondary objectives were to estimate the efficiency and the appropriateness of the use of the resources associated with the intervention and its effects on other relevant outcomes.

The third objective was to define a statistical model able to predict in-hospital death and unscheduled re-admission.

A follow up study to evaluate the effectiveness of the intervention after three years from baseline was described in a separate protocol.

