### Study evaluations

The primary outcome measure is in-hospital mortality. We will also analyze the impact of the clinical pathways comparing the length and the appropriateness of the stay, the rate of unscheduled readmissions, the customers' satisfaction and the costs treating the patients with the pathways and with the current practice along all the observation period. The quality of the care will be assessed by monitoring the use of diagnostic and therapeutic procedures during hospital stay and by the use of key quality indicators at discharge, as reported in previous studies [18-22]. The list of process and outcome indicators is reported in Table 1.

**Table 1 T1:** The indicator set.

**Indicator (measure)**	**Typology**	**Criterion met/expected change**	**Measure**
In hospital mortality	Outcome	Differences in rates	%
Length of hospital stay	Outcome	Differences in mean values	days
Appropriateness of the stay (with Appropriateness Evaluation Protocol – AEP)	Outcome	Differences in rates	%
Costs of the stay (with Activity Based Costing – ABC)	Outcome	Differences in mean values	€ (euro)
Rate of unscheduled readmissions (within 31 days)	Outcome	Differences in rates	%
Patients' satisfaction (survey with 16 items questionnaire)	Outcome	Differences in mean values	score (1–10)
Diagnostic procedures during hospital stay	Process	Differences in rates	%
*Echocardiography*			
*Trans-oesophageal echocardiography*			
*Electrocardiography*			
*Chest x-rays*			
*Oximetry*			
*Weight monitoring*			
*Diuresis monitoring*			
Medical treatment during hospital stay	Process	Differences in rates	%
*Inotropes*			
*ACE-inhibitors*			
*Beta-blockers*			
*Diuretics*			
*Nitrates*			
*Other vasodilators*			
*Heparin*			
*Oral anticoagulants*			
*Anti-platelets agents*			
Left ventricular function (LVF) assessment rate at discharge (or planned for after discharge)	Process	Given to all patients	%
Rehabilitation rate at discharge (or planned for after discharge)	Process	Given to all patients	%
Advice/counseling rate for smoking cessation at discharge	Process	Given to all patients (current smokers)	%
Written instructions rate at discharge (activity level, diet, discharge medications, follow up, weight monitoring and what to do if symptoms worsen)	Process	Given to all patients	%
ACE-inhibitor rate at discharge (without contraindications, with LVF < 40%)	Process	Given to all patients	%

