### Study sample

The sample included all the patients treated by the hospitals during the experimental period with a principal diagnosis of heart failure (all ICD-9CM codes included in 428.xx code). We calculated the sample size needed to detect a statistical difference in the mortality rate. Since in Italy the in-hospital mortality rates range from 5% to 17%, we expected that clinical pathways succeeded to control mortality to 5% to be clinically relevant [23-25]. Based on this goal a sample size of 424 patients (212 in each group) was required for the study to have 80% power at the 5% significance level (two-sided). The sample size calculation was performed according to standard criteria for cluster randomized trials. We adjusted the sample size using an inflation factor of 1.51 to account for the cluster randomization: 7 clusters per trial arm, cluster size of 30 patients, ICC of 0.018 [26-29].

At baseline we verified the comparability of the two groups at the admission measuring patients' age, sex, co-morbidities, risk factors and symptoms severity (Table 2). Patients with a current AMI or unstable angina were excluded from the study.

**Table 2 T2:** Characteristics of 429 Hospital Patients in the Clinical Pathway and Usual Care Study Groups (demographics, risk factors and disease severity at admission).

**Variable**	**Clinical pathway **(n = 214)	**Usual Care **(n = 215)	**p value**
Male gender	102	110	0.50
Mean age in years (SD)	81.7 (8.3)	79.6 (8.5)	0.011
*Admitted from*			
General practitioner	106	109	0.77
Home	108	106	
*Severity at admission*			
NYHA II	16	15	
NYHA III	117	114	0.87
NYHA IV	81	86	
*Co morbidities*			
Hypertension	154	161	0.58
COPD	52	58	0.58
Diabetes	41	38	0.71
Smoking	34	31	0.68

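### Age adjustment is planned only for death and readmission; the tests named for the other arm comparisons cannot adjust for age, although pathway patients are 2.1 years older

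*Protocol article*

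**What the plan says.** The Study evaluations section plans arm comparisons well beyond mortality: "comparing the length and the appropriateness of the stay, the rate of unscheduled readmissions, the customers' satisfaction and the costs", together with the process indicators in Table 1. Several of these serve the aims in the Objectives section: "Secondary objectives were to estimate the efficiency and the appropriateness of the use of the resources".

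The Data analysis section names two kinds of method.

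- **Regression.** It states that "the differences in the rate of in-hospital deaths and unscheduled admissions across groups and according to each variable under study will be evaluated using random-effects" models of the logistic type. Covariates are kept by backward selection at the 0.10 level, "with the exception of age which will be forced to entry".
- **Simple tests.** It also names "common descriptive statistics (Fisher exact and Kruskal Wallis test for categorical and continuous variables, respectively), that will be performed at the cluster level".

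No other method is named for the remaining Table 1 outcomes.

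The Study sample section says "At baseline we verified the comparability of the two groups at the admission" and refers to Table 2. That table gives mean age 81.7 years (SD 8.3) in 214 pathway patients and 79.6 years (SD 8.5) in 215 usual-care patients, p = 0.011. Every other p value in the table is 0.50 or higher.

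**The concern.** Age is the one covariate the plan will not leave to a selection rule, so the plan already treats it as prognostic. Yet it enters only two models. Fisher's exact test and the Kruskal-Wallis test have no place for a covariate, so the other outcomes are compared as they stand, with older patients in the pathway arm.

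Working at the cluster level deals with the correlation of patients within hospitals. It does not remove the age gap, because hospital averages still contain it.

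What is at stake is the reading of the secondary outcomes. If older patients stay longer, cost more or receive less discharge care, the unadjusted comparison is tilted against the pathway and can hide a real benefit. If an outcome moves the other way with age, the tilt favours the pathway. With only 7 hospitals per arm, chance differences in case mix of this size are to be expected, and power to absorb them is limited.

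**Working it through.** **1. Reproducing the age comparison (inputs from Table 2).**

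- Difference = 81.7 − 79.6 = 2.1 years.
- SE = √(8.3²/214 + 8.5²/215) = 0.811, so t = 2.1/0.811 = 2.59 and p = 0.010 at patient level; 95% CI 0.5 to 3.7 years.
- The means are rounded, so the true difference lies between 2.0 and 2.2 years, which gives p = 0.014 to 0.007. The printed 0.011 is reproduced as a test that ignores clustering.
- Pooled SD = 8.40, so the standardised difference is 2.1/8.40 = 0.25.

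**2. Allowing for clustering.** The Study sample section gives the planning values: "inflation factor of 1.51 to account for the cluster randomization: 7 clusters per trial arm, cluster size of 30 patients, ICC of 0.018". That ICC was set for the mortality calculation; using it for age is an assumption.

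- Mean cluster size = 429/14 = 30.6.
- Design effect = 1 + (30.6 − 1) × 0.018 = 1.534.
- t = 2.59/√1.534 = 2.09; on 12 df, p = 0.059.
- At an assumed ICC of 0.05 the design effect is 2.482, t = 1.64 and p = 0.13.

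**3. Shift carried into an unadjusted comparison.** If a continuous outcome has within-arm correlation r with age, the arm difference moves by 0.25 × r SD. The documents give no value for r, so a range is shown. The SE of a standardised arm difference is √(2 × 1.534/214.5) = 0.120. Error and power come from the noncentral t distribution with 12 df (two-sided 5%). Power is for an assumed true benefit of 0.3 SD that the age effect opposes; with no age effect it is 64%.

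| Assumed r | Shift (SD) | Shift (SE) | Conditional error | Power |
|---|---|---|---|---|
| 0.05 | 0.012 | 0.10 | 5.1% | 60% |
| 0.1 | 0.025 | 0.21 | 5.4% | 56% |
| 0.2 | 0.050 | 0.42 | 6.7% | 49% |
| 0.3 | 0.075 | 0.63 | 8.9% | 41% |

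**4. Sensitivity to the ICC.** A larger ICC widens the SE, so the same shift matters less. At ICC 0.05, r = 0.2 gives a conditional error of 6.1%, and at r = 0.1 power falls from 44% to 38%. At ICC 0.10, r = 0.2 gives 5.7%.

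**5. Binary indicators.** The shift on the logit scale is ln(OR per 10 years) × 0.21. For assumed odds ratios of 1.2 to 2.0, an indicator at 50% moves by 1.0 to 3.6 percentage points and one at 10% by 0.3 to 1.4 points.

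**6. Check with the named test.** In simulated trials of 14 hospitals (ICC 0.018, age gap fixed at 2.1 years, no arm effect), the Kruskal-Wallis test on hospital averages rejected in 5.8%, 6.4% and 8.1% of trials for r = 0.1, 0.2 and 0.3. On hospital averages of age-adjusted residuals it rejected in 5.3%, 5.3% and 5.0%.

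**The case against.** The strongest reply is that the article calls these tests descriptive and presents them alongside the regression. It does not say that they are the final analysis of length of stay or cost, and it does not rule out adjusted models. A journal article condenses a fuller plan, which may adjust. This stands as a limit: the point concerns the methods the article names, and one sentence would settle it if age adjustment is already intended.

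Four stronger readings are tempting, and the documents do not support them.

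- *The age gap shows faulty randomisation.* The 0.011 ignores clustering. At about 0.06 or higher on 12 df, the gap is compatible with chance.
- *The design is biased.* Over repeated randomisations the age gap averages out, so it does not bias the unadjusted comparison. The error rates above are conditional on the gap seen in this trial.
- *The article hides the imbalance behind its statement on comparability.* That statement can be read as saying that comparability was checked, and Table 2 prints the age difference and its p value.
- *NYHA class must be adjusted for as well.* It is balanced in Table 2 (p = 0.87) and is not forced even into the mortality model.

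It is also fair to say that choosing covariates by baseline p values is poor practice, and that for some process indicators, such as those meant for every patient, age may hardly matter. Neither removes the point. The reason to adjust is that the plan itself treats age as prognostic, and a chance gap in a prognostic variable still moves this trial's estimates.

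**Conclusion.** The point holds in limited form. The plan controls age for two outcomes and, for the remaining Table 1 comparisons, names only tests that cannot do so, while its own Table 2 shows a 0.25 SD age difference between arms. In-hospital mortality, the primary outcome, and readmission are untouched.

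The size depends on age-outcome correlations that the documents do not give. At r = 0.05 the effect is negligible on error and small on power. At r = 0.3 it is material, and the larger cost there is lost power for a benefit that age opposes. These figures also assume an ICC of 0.018 for every outcome and a 0.3 SD benefit. With a higher ICC the shift is smaller relative to the SE, and low power then comes mainly from having 14 clusters. The direction can differ between outcomes. The change is worth making because age is already collected and the plan already adjusts for it elsewhere.

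**What to change.** In the Data analysis section, extend the age adjustment used for death and readmission to the other Table 1 arm comparisons, at least length of stay, cost and appropriateness of stay. Either of two methods would do:

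- a random-effects model with arm and age, of a type suited to the outcome; or
- a patient-level regression of the outcome on age without the arm, followed by a comparison of the hospital means of the residuals, 7 against 7, which keeps the cluster-level approach.

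Keep the unadjusted Fisher and Kruskal-Wallis tests as descriptive. Give age's prognostic role as the reason, not the Table 2 p value. Adjustment for NYHA class is optional, and the Study sample section may note the 2.1-year difference.

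The cost is some extra analysis work and an assumption about the form of the age effect. No new data or patients are needed, and the sample size does not change.

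### The Fisher exact test named at cluster level does not fit hospital percentages, and the p-values in Table 2 were not produced at that level

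*Protocol article*

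**What the plan says.** The Data analysis section names two tests and their level: "Fisher exact and Kruskal Wallis test for categorical and continuous variables, respectively), that will be performed at the cluster level". It introduces them as descriptive statistics.

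The same sentence then gives a model that allows for hospital, but for two outcomes only: "the differences in the rate of in-hospital deaths and unscheduled admissions across groups" "will be evaluated using random-effects logistic regression, thus accounting for the clustering effect". The threshold follows without restriction to any outcome: "Statistical significance will be defined as a two-sided p-value < 0.05".

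The list of comparisons is longer. Study evaluations says "We will also analyze the impact of the clinical pathways comparing the length and the appropriateness of the stay", and goes on to satisfaction, costs and quality-of-care measures. Apart from death and readmission, Table 1 lists:
- one further outcome rate (appropriateness of stay);
- three means (length of stay, cost, satisfaction);
- 21 process rates (7 diagnostic, 9 treatment, 5 at discharge).

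On baseline, Study sample says "At baseline we verified the comparability of the two groups at the admission", and Table 2 gives p-values for 214 versus 215 patients.

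**The concern.** Two things do not fit together.

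First, Fisher's exact test needs counts of independent units. If the unit is the hospital, each Table 1 rate becomes one percentage per hospital. That is a continuous quantity, and Fisher does not apply to it unless each hospital is classed as, say, high or low. The article states no such cut.

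Second, the article already reports p-values, and they appear to have been computed on patients. That departs from the level that Data analysis states.

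At stake are the 22 rates for which no model with a hospital effect is named. Read literally, the plan gives them a coarse, weak test. Run as Table 2 seems to have been, they would get a test that treats patients of one hospital as independent, which in a hospital-randomised trial rejects too often.

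**Working it through.** **Inputs.** Table 2: patient counts and p-values, 214 versus 215. Study sample: "inflation factor of 1.51 to account for the cluster randomization: 7 clusters per trial arm, cluster size of 30 patients, ICC of 0.018". Data analysis: two-sided 0.05.

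**Step 1. Reproduce Table 2 with Fisher on patient counts.**

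| Row | Counts | Stated p | Fisher | Chi-square | Yates |
|---|---|---|---|---|---|
| Male | 102 / 110 | 0.50 | 0.4996 | 0.469 | 0.530 |
| COPD | 52 / 58 | 0.58 | 0.581 | 0.525 | 0.600 |
| Diabetes | 41 / 38 | 0.71 | 0.710 | 0.692 | 0.786 |
| Smoking | 34 / 31 | 0.68 | 0.688 | 0.671 | 0.772 |
| Hypertension | 154 / 161 | 0.58 | 0.513 | 0.493 | 0.565 |
| Admitted from GP | 106 / 109 | 0.77 | 0.847 | 0.809 | 0.885 |
| NYHA (3 classes) | 16, 117, 81 / 15, 114, 86 | 0.87 | 0.909 | 0.896 | – |

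Three rows match patient-level Fisher to two decimals. Smoking is within 0.01. Hypertension, source of admission and NYHA match none of these tests.

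**Step 2. What could a hospital-level Fisher test give?** With 7 hospitals per arm and any dichotomy, the attainable two-sided p-values are 0.0006, 0.0047, 0.021, 0.029, 0.070, 0.103, 0.192, 0.266, 0.286, 0.462, 0.559, 0.592 and 1. None of 0.50, 0.58, 0.68, 0.71 or 0.77 is among them. For NYHA, hospitals sorted into three classes give no value between 0.8 and 1, so 0.87 is also unattainable.

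The coarseness also shows the low power:
- 5 hospitals versus 0: 2 × C(7,5)/C(14,5) = 2 × 21/2002 = 0.021.
- 6 versus 1: 2 × (49 + 1)/3432 = 0.029.
- 4 versus 0: 2 × 35/1001 = 0.070, not significant.

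**Step 3. Could Table 2 come from a rank test on 14 hospital percentages?** The untied asymptotic Kruskal-Wallis values around the stated figures are 0.482, 0.565, 0.655, 0.749 and 0.848, so none fits. An exact untied rank test can give 0.710, which agrees with diabetes, but its neighbouring values (0.456, 0.535, 0.620, 0.805, 0.902) fit no other row. Male gender and COPD are therefore the rows that point specifically to patient-level Fisher.

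**Step 4. Size of an unadjusted patient-level test.** Design effect = 1 + (30 − 1) × ICC. True size ≈ 2 × [1 − Φ(1.96/√design effect)].

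| ICC | Design effect | Formula | Simulated Fisher |
|---|---|---|---|
| 0.018 (plan) | 1.522 | 2 × [1 − Φ(1.589)] = 0.112 | 0.08–0.09 |
| 0.05 (assumed) | 2.45 | 2 × [1 − Φ(1.252)] = 0.210 | 0.16–0.19 |
| 0.10 (assumed) | 3.90 | 2 × [1 − Φ(0.992)] = 0.321 | 0.28–0.30 |

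The simulations used 14 hospitals of 30 patients and event rates of 10% and 50%. Fisher lies below the formula because it is conservative. The plan's rounded factor of 1.51 gives 0.111. A t-test on the 14 hospital values kept a size of about 0.044 to 0.055 throughout.

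**The case against.** The strongest reply is that the plan says the opposite of what is feared. Tests on hospitals as units do not have the patient-level inflation, and a dichotomised 7-versus-7 Fisher errs towards too few rejections. That stands for the plan as worded. The inflation figures apply only if practice follows Table 2.

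Kruskal-Wallis on 14 hospital means, or on 14 hospital percentages, is also a valid cluster-level test. That stands fully: the misfit concerns Fisher, and Kruskal-Wallis need not be dropped.

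The Table 2 evidence has limits too. Three of its seven categorical rows do not reproduce, and the diabetes match does not discriminate. Nor does age: a patient-level t-test on 81.7 (8.3) versus 79.6 (8.5) gives t = 2.59, p = 0.010 (0.007 to 0.014 given rounding of the means), against 0.011 stated, but an exact rank test on 7 versus 7 hospitals can also give 0.011. These points weaken the identification of the test. They do not rescue the stated level for the categorical rows, since no row is attainable from a hospital-level Fisher test.

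A reader might infer that every secondary outcome will be tested on patients as if independent. The document does not support that. Table 2 is a baseline table, the tests are called descriptive, and a fuller plan may name other methods for these indicators. A reader might also say that the age imbalance vanishes once clustering is allowed for (p about 0.06 with design effect 1.53 and 12 degrees of freedom). That borrows the ICC of 0.018 from the mortality calculation. No ICC for age is given, and age is forced into the regression models whatever its p-value.

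**Conclusion.** The point holds in limited form. The stated rule, Fisher at hospital level, is ill-defined for the Table 1 rates, and its only reported use contradicts it. This is an inconsistency within the article and not an omission that an unseen analysis plan would excuse.

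The consequence is conditional. If the rates without a named cluster model were tested on patients, the true size would be about 8–11% at ICC 0.018. It would be roughly 16–21% at 0.05 and 28–32% at 0.10. Only the first ICC is the plan's, and that one was set for the mortality calculation; the other two are assumptions.

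In-hospital mortality and unscheduled readmission have a random-effects model, so nothing here touches the primary conclusion. It should be fixed, but it does not threaten the trial.

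**What to change.** - **Table 1 rates other than death and readmission:** replace cluster-level Fisher with a logistic model with arm as fixed effect and hospital as random intercept, or with a t-test or rank test on the 14 hospital percentages.
- **Length of stay, cost and satisfaction:** keep Kruskal-Wallis, stating that it is applied to the hospital means, or use a mixed model with a hospital effect.
- **Table 2:** remove the p-values or replace them with ones that allow for hospital. If any stay, say which test produced each one and recheck hypertension, source of admission and NYHA.

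The cost is a few sentences of text and some re-analysis with standard methods; no new data are needed. Intervals will be wider than unadjusted patient-level ones, as the hospital randomisation requires.

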### Study design

We performed a cluster multi-centre randomized controlled clinical trial to evaluate the effect of applying clinical pathways to process and outcome indicators and to the costs sustained to assist the patients with heart failure. We compared the results obtained treating the patients with clinical pathways to the results obtained with the usual care. Since a clinical pathway is not a single intervention to be compared with a placebo but its eventual benefits come from a mix of complex actions that are implemented at the institutional level (appropriate use of practice guidelines and supplies of drugs and ancillary services, new organization and procedures, patient education, etc.), we randomly assigned hospitals, rather than individual patients, to either introduce the pathway or continue usual care [13-17].

Forty hospitals based in four Italian Regions were invited to participate to the study (Figure 1). Eighteen hospitals showed interest in the implementation of the clinical pathway for the hospital treatment of heart failure and were assessed for eligibility. Of the eighteen hospitals that asked to implement the clinical pathway for heart failure we selected and randomized fourteen community hospitals. We based the selection on the comparability of their location, patient population, facilities and teaching status (mean bed size of the hospitals assigned to clinical pathways was 245, in the usual care group was 262).

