## Discussion

Even though randomized controlled trials are widely accepted as the most reliable method of determining effectiveness, clinical pathways has not been studied sufficiently in this way. Typically controlled trial design is not used in evaluating clinical pathways because the context level adaptation, which is essential for pathways to work, is perceived as inappropriate in the trial design, likely for the difficulty of keeping replicable and recognizable the intervention [36]. According to Hawe we think that a controlled trial design is appropriate to evaluate clinical pathways as well as other complex interventions and that it is possible to standardize the intervention (the clinical pathways) effectively. To this purpose we defined as standard the steps in the change process or the key functions that the elements of the intervention were meant to improve according to each context. Also the definition of the quality care indicators helped. The indicators were driven by the theory and concerned the functions provided by the key elements of the intervention that were based on expected adherence to the same evidences. We think that this strategy based on combining local change standards to the use of shared evidence based indicators kept the integrity of the intervention in each site.

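### The covariate rule for the death and readmission models is not limited to admission variables, so care that the pathway is meant to change can be selected into the model that estimates the pathway effect

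*Protocol article*

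**What the plan says.** The protocol article's Data analysis section states that "the differences in the rate of in-hospital deaths and unscheduled admissions across groups and according to each variable under study will be evaluated using random-effects" models, of logistic form. The selection rule follows: "Variables will be included if significant at the 0.10 level (backward approach), with the exception of age which will be forced to entry". Study arm is not named as forced in, no candidate list is given, and nothing restricts candidates by time of measurement. Patients who died are excluded from the readmission model.

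Two sets of quantities are studied. Table 2 holds admission characteristics; the Study sample section says "At baseline we verified the comparability of the two groups at the admission measuring patients' age, sex, co-morbidities, risk factors and symptoms severity". Table 1 holds the indicator set, and the Study evaluations section says "The quality of the care will be assessed by monitoring the use of diagnostic and therapeutic procedures during hospital stay". The Study design section gives the aim as "to evaluate the effect of applying clinical pathways to process and outcome indicators", and the Discussion says that the indicators "concerned the functions provided by the key elements of the intervention". The Intervention section counts diagnostic exams and medical treatments among the pathway's care categories.

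The Objectives section has a third aim, a model predicting in-hospital death and unscheduled readmission. The Data analysis section describes one selection procedure for those outcomes and does not say whether it serves that aim, the comparison of arms, or both.

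**The concern.** The primary question is whether the pathway lowers in-hospital mortality. A covariate measured after admission, and changed by the pathway, harms that comparison in two ways.

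- **Mediation (both models).** Holding received care fixed removes whatever benefit comes through that care. What is left is a direct effect, which is not what the Objectives section asks for.
- **Receipt depends on survival (mortality model only).** A patient who dies soon after admission has less time to be recorded as having had a test or drug, and a patient who dies in hospital cannot receive a discharge item. Even an inert item can then look protective. If the pathway raises its use, adjustment shifts the arm effect against the pathway.

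The covariate rule governs the primary outcome, so either mechanism could hide a real benefit or suggest a harm that does not exist.

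**Working it through.** The plan gives no figure on this point to reproduce. The check is a reading of the text followed by illustrations. **All uptake, timing and item-specific death rates below are assumptions; none comes from the article.**

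**1. What the wording can admit.** Table 1 has 7 in-hospital diagnostic items, 9 in-hospital drug items and 5 discharge items typed as process: 7 + 9 + 5 = 21. Table 2 has 8 variables (sex, age, source of admission, NYHA class, hypertension, COPD, diabetes, smoking). On the widest reading there are 21 + 8 = 29 candidates. On the narrowest there are 8.

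**2. Mediation.** Suppose the pathway acts only through one item, received by 50% of control and 80% of pathway patients, with mortality 20% without it and 5% with it.
- Control: 0.5 × 0.05 + 0.5 × 0.20 = 12.5%
- Pathway: 0.8 × 0.05 + 0.2 × 0.20 = 8.0%
- Total-effect odds ratio: (0.080/0.920) / (0.125/0.875) = 0.61
- With the item in the model: 1.00 by construction, since mortality depends only on the item

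A simulation of 400,000 patients gave 0.60 and 0.99. With uptake of 50% vs 70% it gave 0.74 and 1.00; with 40% vs 90%, 0.42 and 0.97.

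**3. Receipt depends on survival.** Let mortality be p in both arms (no pathway effect), intended uptake m, and e the fraction of deaths too early to receive an inert item.
- Odds of death with the item: p(1 − e)m / [(1 − p)m] = p(1 − e)/(1 − p), the same in both arms, so odds ratio 1.
- Odds of death without the item: p[1 − (1 − e)m] / [(1 − p)(1 − m)].

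With p = 0.13, e = 0.3 and m = 0.5 vs 0.8, the odds without the item are:
- Control: 0.13 × 0.65 / (0.87 × 0.5) = 0.194
- Pathway: 0.13 × 0.44 / (0.87 × 0.2) = 0.329
- Ratio: 1.69

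The adjusted model averages 1 and 1.69; the simulation gave 1.32. Over e = 0.3 to 0.5 and uptake from 50% vs 70% to 40% vs 90%, the adjusted null odds ratio ran from 1.17 to 2.54.

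**4. Dependence on timing.** Assumptions: inert item; uptake 60–70% control, 90% pathway; death day exponential with mean 4–5 days, wrapped to a 10-day stay; item done uniformly over a window after admission. Adjusted arm odds ratios from expected cell frequencies:

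| Window | Deaths before the item would be done | Mortality 10% vs 10% (true 1.00) | Mortality 15% vs 5% (true 0.30) |
|---|---|---|---|
| half a day | about 6% | 1.06–1.09 | 0.31–0.32 |
| 1 day | 11–13% | 1.12–1.18 | 0.33–0.34 |
| 6 days | 48–53% | 1.62–2.00 | 0.46–0.55 |

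Simulated runs gave values as low as 1.05 at half a day, hence the rounded range of 1.05 to 2.0.

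**5. Discharge items, the limiting case.** In-hospital deaths receive none, so e = 1. There are no deaths among recipients, and the arm effect comes from non-recipients alone: a null odds ratio becomes (1 − m0)/(1 − m1), for example 0.5/0.2 = 2.5 with 50% vs 80% of survivors receiving the item.

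**6. Readmission model.** Deaths are excluded, so steps 3 to 5 do not apply. Only step 2 does.

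**The case against.** The strongest reply is that the article never says it will adjust for process items. Table 1 calls its entries indicators and sets them out for comparison between arms. Table 2 is the table headed by variables, and age, the one covariate named in the rule, is in it. So an admission-only reading is possible, and an unseen analysis plan may adopt it. Backward selection with checks for interactions and higher powers also suits the prediction objective, where later information can be legitimate.

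This stands in part. It rules out four stronger conclusions that a reader might draw:

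- *The plan does adjust for post-admission care.* Candidates are not named, and an item affects the final model only if it survives the 0.10 step. At an assumed 15% vs 5% mortality, only about 212 × 0.15 + 212 × 0.05 = 42 deaths are expected, so survival of any given item is uncertain.
- *Every process item would look protective.* Drugs given to sicker patients, such as inotropes, may look harmful.
- *Early death biases both models.* It cannot act in the readmission model, which excludes deaths.
- *The null odds ratio would be 1.6 to 2.0.* In the timing example that needs an item spread over six days. Oximetry, electrocardiography and chest x-ray may well be done on arrival, where the shift is small.

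The reply does not remove the point. The article states the selection method, threshold, forced covariate and candidate pool, and the pool has no time limit. The admission-only restriction has to be supplied by the reader.

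**Conclusion.** The concern holds as a fault in a stated rule. Followed on its plain wording, the rule allows data-driven selection to put consequences of the intervention into the model for the primary outcome, and the same procedure appears to serve both estimation and prediction.

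The possible size is material: a benefit acting wholly through one item can vanish (0.61 to 1.00), and in the mortality model a null effect can become about 1.05 to 2.0 for an in-hospital item, with larger shifts under more extreme uptake or for discharge items. These figures show direction and plausible scale under assumed inputs. They do not predict this trial's result. For readmission, only the mediation argument applies.

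**What to change.** In the Data analysis section:

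1. Estimate the pathway effect on in-hospital death and on readmission with study arm kept in the model and only pre-specified covariates measured at or before admission (Table 2: age, sex, source of admission, NYHA class, co-morbidities, smoking).
2. Analyse the Table 1 process items as outcomes compared between arms, not as covariates for the arm effect.
3. Describe the prediction models of the third objective separately. The in-hospital death model should not use discharge items or care whose receipt depends on survival. A readmission model applied at discharge may use information known by then, so a blanket ban on post-admission data there would go too far.

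The cost is a few sentences. No new data are needed and the sample size does not change.
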